# Integral movement therapy versus local movement therapy approach in patients with idiopathic chronic low-back pain: study protocol for a randomized controlled trial

**DOI:** 10.1186/s13063-018-3128-z

**Published:** 2019-01-21

**Keywords:** Chronic low-back pain, Integral movement therapy, Local movement therapy, Supervised training

## Abstract

**Background:**

Chronic low-back pain (CLBP) is one of the most common reasons for seeking medical care and it imposes a significant burden on individuals and society at large. Systematic reviews evaluating the effectiveness of supervised exercise therapies commonly conclude that, to date, there is no evidence to support the superiority of one form of exercise over another. Randomized controlled trials (RCT) to date included mostly trunk strengthening exercises (e.g. bird dog, plank) and there is no evidence about supervised, individually graded integral movement therapy program for patients with CLBP.

**Methods:**

The research design is a RCT with parallel-group design including two intervention groups: integral movement therapy and conventional local movement therapy. Participants in each group will receive 20 supervised sessions in a 10-week period, twice per week, for approximately 1 h per session. Outcome assessments will occur at baseline and immediately after intervention, follow-up will take place at six months and 12 months after the intervention. Prespecified analyses will evaluate the main effects of the treatment.

**Discussion:**

This trial will use a novel, previously unexplored integral approach to CLBP through exercises. In contrast to commonly used exercise programs, the integral program does not include specific local strength exercises for hip and trunk flexors and extensors. However, learning dynamic trunk muscle control in various body positions with added limb movements could be beneficial because of the parallels to everyday work. The study will contribute to clinical practice by providing evidence to guide professionals when deciding for the proper and efficient treatment of patients with CLBP.

**Trial registration:**

ClinicalTrials.gov, NCT03623802. Registered on 9th August 2018.

**Electronic supplementary material:**

The online version of this article (10.1186/s13063-018-3128-z) contains supplementary material, which is available to authorized users.

## Background

Chronic low-back pain (CLBP) is one of the most common reasons for seeking medical care and it imposes a significant burden on individuals and society at large. The lifetime prevalence of low-back pain (LBP) is up to 84%. After an initial episode of LBP, 44–78% of people suffer relapses of pain and 26–37% relapses of work absence [1].

Literature suggests several different methods for coping with CLBP [1]. Supervised exercise therapies are among the most commonly advocated treatments for non-specific CLBP [1]. However, findings from a systematic review concluded the most effective model of exercise therapy remains uncertain [1]. Although several supervised randomized controlled trials (RCT) focusing on different approaches for managing the CLBP using movement therapy have been published so far [2–8], there is no evidence about integral movement therapy program for patients with CLBP. Systematic reviews evaluating the effectiveness of supervised exercise therapies commonly conclude that, to date, there is no evidence to support the superiority of one form of exercise over another [9, 10]. RCTs to date include mostly trunk-strengthening exercises (e.g. bird dog, plank) [5, 7, 8, 11, 12].

People with CLBP often report an impaired ability to perform daily activities. LBP can lead to a significant level of disability and physical functioning [13]. It is common for CLBP patients to avoid activity due to the fear of further exacerbating the pain or harming the spine [14]. LBP is correlated with weak core muscles and delayed muscle activation [15]. In accordance with that, we propose an integral movement therapy program, which is focused on simulating the most common daily activities, body positions, and movements, which require coordinated contraction of local and superficial muscles. Developed with expert consensus, this intervention is based on exercise progression (i.e. from stable to unstable body positions, from single-plane to multi-plane movements, and from minimal resistance/load to maximal). The main focus with all exercises and stages is the control of core/spine position.

## Methods/ design

### Aims and research questions

The primary study aim is to evaluate the efficiency of supervised and individually graded integral movement therapy program in patients with CLBP on pain, quality of life, and functional abilities. Further, the secondary aim is to compare the difference in outcome measures to supervised, conventional local movement therapy. The following research questions are addressed:Does the supervised and individually graded integral movement therapy program have an effect on reducing pain, improving the quality of life and functional abilities in patients with idiopathic CLBP?Does the supervised and individually graded integral movement therapy program have a clinically more significant effect on reducing pain, improving the quality of life and functional abilities compared to the supervised, conventional local movement therapy?Which program has a better effect on specific core stability strength (e.g. maximal isometric trunk flexion, extension and lateral flexion) and proprioception?

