### Trial design and study setting

The research design is a superiority RCT with parallel-group design allocating patients 1:1 to either integral movement therapy or conventional local movement therapy. Intervention protocol was prepared and revised by group of physiotherapy and kinesiology experts in February 2018.

The executive researcher will be Assoc. [name]. Sc. [name], grad. Physioth., grad. Phys. edu. Teacher, who will communicate with other investigators, trial participants, and journals if there will be any important protocol modifications; the executive medical doctor will be [name], GP; and the responsible kinesiologist who will carry on the practical part of the intervention will be [name], BSc (PE).

We intend to allocate 80 adults, aged 30–60 years, into two groups. Repeated measurements will be performed at baseline and after therapy. Follow-up measures will take place six months and one year after the last therapy and include an International Physical Activity Questionnaire (IPAQ), qualitative and quantitative assessment of pain with the Oswestry Disability Index (ODI) questionnaire and the Numerical rating scale (NRS), 0–10 (see the Standards Protocol Items: Recommendations for Interventional Trials (SPIRIT) flow chart; Fig. 1). All steps and tools of the study protocol have been described adhering to the SPIRIT Check list (Additional file 1).

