## Participants

### Recruitment

Potential participants will be identified and recruited to the trial by general practitioners who work in the healthcare center in Kranj. Patients who seek medical help due to idiopathic CLBP which persists for at least 12 weeks [1] or had at least two acute episodes of LBP in the last 12 months and fulfill the inclusion and exclusion criteria will be referred to a responsible researcher. A researcher will approach the potential participant and inform them of all aspects of the study and provide a written information sheet, which will state that participation is voluntary and that they are free to withdraw at any time without affecting subsequent medical care (Additional file 3). Personal results and treatment summary will be available at the end of the trial to each participant on individual consultation.

There are no expected contraindications during the treatment protocol, except increased LBP, which can arise in some individuals. If so, according to a consultation with the medical doctor and executive researcher, the load and intensity of exercises will be decreased. If the pain exacerbates, the patient will discontinue the program.

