## Discussion

The purpose of this RCT is to determine if individually graded integral movement therapy program is more effective than the widely used conventional local movement therapy program for treating patients with non-specific CLBP. This trial will use a novel, previously unexplored integral approach to CLBP through exercises. In contrast to commonly used exercise programs [5, 7, 8, 11, 12], the integral program does not include specific local strength exercises for hip and trunk flexors.

The proposed integral program is based on functional exercises with focus on trunk stability with additional single- or multi-planar limb movements. In the first few sessions, body positions are stable and limb movements are simple with minimal or without external load. The first goal is to teach participants about proper core activation in everyday body positions and movements and to build up basic proprioception, endurance, and strength. Further on, more complex tasks in less stable body positions demand more coordination and specific strength from the participant to perform it in the right way (i.e. without any compensatory movements).

It may be argued that starting a movement therapy program in an integral way is inappropriate as weak trunk muscles and delayed muscle activation are usually the main reasons for pain in patients with non-specific CLBP [15]. However, learning dynamic trunk muscle control in several body positions with added limb movements could be beneficial because of the parallels to everyday work. Literature suggests that dynamic trunk muscle control is modified during LBP remission and in patients with CLBP [28–30]. This is why learning and training core muscles in an integral way can be superior to local strengthening of the core.

As this intervention requires no expensive equipment (elastic bands and Swiss ball, optional weights), it is suitable to perform at any physiotherapy or kinesiology department. Furthermore, when patients learn to perform the exercises, they can continue performing it at home with no extra costs. The study will contribute to clinical practice by providing evidence to guide professionals when deciding the proper and efficient treatment of patients with CLBP. The results of this study will be published once the study is concluded.

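### The primary aim asks about the integral programme alone and ranks the randomised comparison second, which contradicts the superiority design and the purpose given in the Discussion

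*Protocol article*

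**What the plan says.** In the protocol article, Aims and research questions, the first aim reads: "The primary study aim is to evaluate the efficiency of supervised and individually graded integral movement therapy program in patients with CLBP". The outcomes attached to it are pain, quality of life and functional abilities. It then says that "the secondary aim is to compare the difference in outcome measures to supervised, conventional local movement therapy". The research questions keep that order. The first asks "Does the supervised and individually graded integral movement therapy program have an effect on reducing pain", with no comparator, and the second asks about integral against local therapy.

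Two other sections put the comparison first. Trial design and study setting describes a "superiority RCT with parallel-group design allocating patients 1:1 to either integral movement therapy or conventional local movement therapy". The Discussion gives the trial's purpose as to "determine if individually graded integral movement therapy program is more effective than the widely used conventional local movement therapy program".

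Data processing and statistical analyses uses repeated-measures analysis of variance to detect change in the functional outcomes from baseline to the end of therapy. It sets P < 0.05 for all tests and applies a 30% minimal important difference both within and between groups. It compares the arms on categorical IPAQ at each time point with a chi-squared test.

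**The concern.** The order of the aims decides which result is the headline. Both randomised arms are exercise programmes and there is no untreated arm. The only comparator is assigned to the secondary aim. What remains for the primary aim is change from baseline in the integral arm, and randomisation gives that quantity no protection.

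Recruitment takes "Patients who seek medical help due to idiopathic CLBP", and the eligibility criteria also admit people with two acute episodes in the past 12 months. Some may enter when their pain is above its usual level. A later fall can then reflect regression to the mean, the natural course, or the attention that comes with 20 supervised sessions. All of these would count towards the primary aim as worded, and two equally effective (or equally ineffective) programmes could both appear to meet it.

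**Working it through.** **1. The texts side by side.** The aims and research question 1 concern the integral programme's own effect, without a comparator. The design section and the Discussion concern integral against local. If the primary aim is read as already comparative, the secondary aim has no separate content. The within-arm reading is therefore an inference, but it is the only one that gives both aims a meaning. The contradiction follows from the text and needs no arithmetic.

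**2. The plan's own figure.** Sample size and sampling procedure gives 40 per group, 80% power and a 30% improvement. It gives no SD, baseline mean, responder rate or sidedness, so 40 cannot be reproduced from its inputs. Worked backwards for a between-arm comparison of means at two-sided 5%:

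δ = (1.960 + 0.842) × √(2/40) = 0.63 SD.

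**3. Illustration of a within-arm test with no treatment effect.** All of these inputs except n = 40 and P < 0.05 are assumptions: pain score normal with mean 4 and SD 2 at both times, within-person correlation r, entry only if the baseline score is at least c, and a two-sided paired t-test counting falls only.

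- α = (c − 4)/2 and λ = φ(α)/(1 − Φ(α))
- baseline mean = 4 + 2λ; baseline variance V = 4(1 + αλ − λ²)
- expected fall = (1 − r) × 2λ
- variance of change = (1 − r)²V + 4(1 − r²)
- d = fall / SD of change; the probability comes from the noncentral t with 39 df and noncentrality d√40

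Worked case, c = 4 and r = 0.5: λ = 0.798, baseline mean 5.60, V = 1.454. Fall = 0.5 × 2 × 0.798 = 0.80, which is 0.80/5.60 = 14%. Variance of change = 0.25 × 1.454 + 4 × 0.75 = 3.363, so the SD is 1.834 and d = 0.435. Probability of a significant fall: 77%.

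| Entry cut-off | r | Mean fall (points) | Fall as % of baseline | Chance of a significant fall |
|---|---|---|---|---|
| none | any | 0 | 0% | 2.5% |
| 3 | 0.8 | 0.20 | 4% | 17% |
| 3 | 0.5 | 0.51 | 10% | 39% |
| 4 | 0.8 | 0.32 | 6% | 36% |
| 4 | 0.7 | 0.48 | 9% | 52% |
| 4 | 0.5 | 0.80 | 14% | 77% |
| 5 | 0.8 | 0.46 | 7% | 64% |
| 5 | 0.7 | 0.68 | 11% | 82% |
| 5 | 0.5 | 1.14 | 18% | 97% |

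**4. The same question without an entry rule.** If the natural change is expressed directly in SDs of change, the chance with 40 patients is 23% at 0.2 SD, 46% at 0.3 SD, 69% at 0.4 SD and 87% at 0.5 SD. If both arms share that change, the two-sided between-arm test stays at 5%.

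**The case against.** The comparative intent is not lost. The title, the design section, the Discussion and research questions 2 and 3 are all comparative, and IPAQ is compared between arms. The fault lies in the ranking within one section. This stands. It argues against calling the trial uncontrolled, and it also shows how easily the aims can be brought into line.

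A reader might infer that a false claim of efficacy is close to certain, taking the 77% or 97% as the trial's error rate. The documents do not support that. The eligibility criteria set no minimum pain score, and a patient who qualifies through past episodes may enter with little current pain. With no selection on current pain, regression to the mean vanishes and the chance is 2.5%. No natural-recovery rate is given either, and the Background reports relapse in 44–78% after a first episode. Spontaneous improvement can lower scores here, but nothing shows that it will.

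A reader might also infer that a significant within-arm change is, by the plan's rules, success on the primary aim. No section says so. The plan has a 30% threshold within groups, and every mean fall in the table is below it. In these scenarios the chance that the observed mean fall reaches 30% is below 1%. The threshold limits the concern without removing it, because the analysis section does not make 30% a condition for success.

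Finally, a repeated-measures analysis of two groups would ordinarily include a group-by-time term, and an article may leave that detail to a fuller document. Its absence is not a fault in itself. It means only that the analysis section, as written, does not resolve the conflict over the aims.

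**Conclusion.** The point holds as a contradiction over what the trial's primary question is. As worded, the primary aim and research question 1 can be met only by before-after change in one arm, while the design and the Discussion call for a between-arm comparison. Non-specific improvement can therefore be counted as efficacy when the arms do not differ.

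This conclusion rests on the text. How often it would mislead cannot be fixed from the documents. The illustrative range of 2.5% to 97% depends on the assumed mean, SD, correlation and strength of selection, and shows only that a within-arm test can be far from its nominal level. It does not follow that the randomised result would be set aside or that a before-after claim will be made. The stated hierarchy permits such a claim, and the rest of the article gives no reason to want it.

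**What to change.** Bring the aims into line with the design section and the Discussion:

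- **Primary aim:** the between-arm difference (integral minus local) in the outcomes listed under Primary outcome measures. That section lists three questionnaires and seven functional tests and singles out none, so the aim should refer to that list and not imply one named endpoint.
- **Research question 1:** reword it as the comparative question.
- **Analysis:** state that the repeated-measures analysis tests the between-arm difference in change (group-by-time).
- **Within-arm change:** report it descriptively with confidence intervals, and state that it supports no claim of efficacy.

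Recruitment began in May 2018, so record this as a dated amendment. The registry wording is not in the documents and should be checked for consistency.

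No new data, arms or visits are needed. The easy within-arm claim of effectiveness is lost. The trial's conclusion would then rest on a comparison of two active programmes, for which 40 per arm gives 80% power only at about 0.63 SD (two-sided 5%).

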### Trial design and study setting

The research design is a superiority RCT with parallel-group design allocating patients 1:1 to either integral movement therapy or conventional local movement therapy. Intervention protocol was prepared and revised by group of physiotherapy and kinesiology experts in February 2018.

The executive researcher will be Assoc. [name]. Sc. [name], grad. Physioth., grad. Phys. edu. Teacher, who will communicate with other investigators, trial participants, and journals if there will be any important protocol modifications; the executive medical doctor will be [name], GP; and the responsible kinesiologist who will carry on the practical part of the intervention will be [name], BSc (PE).

We intend to allocate 80 adults, aged 30–60 years, into two groups. Repeated measurements will be performed at baseline and after therapy. Follow-up measures will take place six months and one year after the last therapy and include an International Physical Activity Questionnaire (IPAQ), qualitative and quantitative assessment of pain with the Oswestry Disability Index (ODI) questionnaire and the Numerical rating scale (NRS), 0–10 (see the Standards Protocol Items: Recommendations for Interventional Trials (SPIRIT) flow chart; Fig. 1). All steps and tools of the study protocol have been described adhering to the SPIRIT Check list (Additional file 1).

**Fig. 1 Fig1:**
[figure not shown]
Schedule of enrollment, interventions, and assessments (Standard Protocol Items: Recommendations for Interventional Trials (SPIRIT) flow chart). IPAQ International Physical Activity Questionnaire, ODI Oswestry Disability Index questionnaire, NRS numeric rating scale, TUG timed up and go test (3 m), CSR chair seat and reach, 6MWT 6-min walk test, BS Biering-Sorensen test, mSCH Modified Schober flexibility test, SRB Sharpened Romberg balance test, Tflex trunk flexion strength, Text trunk extension strength, Tlat trunk lateral flexion strength, REPerror trunk reposition error test, MaxPELincl maximal pelvic inclination at full trunk flexion

This study was approved by the National Medical Ethic Committee. The registration number is 0120–93/2018/6 (Additional file 2), registered on 19 March 2018, https://clinicaltrials.gov/ct2/show/NCT03623802.

The trial will be conducted in the primary healthcare unit in Kranj, the third biggest primary health center in Slovenia, under the Department of Kinesiology with cooperation from the University of Primorska, Faculty of Health Sciences.

### Sample size and sampling procedure

The sample size for this study is estimated based on clinically important improvements in patient measures through an anchor-based approach which was set at ≥ 30% [16]. In this regard, statistical power is considered to be 1-β (80%). Thus, the inclusion of at least 40 patients per group is planned [17]. Participants are allocated in a 1:1 ration to either of the two groups, local or integral, by a sealed envelope randomization system. Once the patient gives consent to enter a trial, an independent person will perform the randomization by picking one envelope out of 80, 40 of each option, and assigning the patient to the group written in the envelope.

Patients are blinded to treatment allocation, although they are informed about receiving exercise therapy without revealing the content of the treatment. Kinesiologists and physiotherapists who perform therapies are not blinded to treatment allocation, but they do not take part in the outcome measurements.

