## Outcome measures

### Primary outcome measures

There are two aspects of primary outcome measures. The first part of the measures is based on different questionnaires: level of disability (ODI questionnaire); physical activity (IPAQ questionnaire); and pain (NRS questionnaire). All questionnaires will be conducted at baseline, immediately after the intervention, and six months and 12 months after finishing the intervention, as medium- and long-term follow-ups. The second part consists of different functional tests: timed up and go test (TUG); sit to stand test; chair seat and reach test (CSR); 6-min walk test (6MWT); Biering Sorensen test (BS); modified Schober test (mSCH); and Sharpened Romberg balance test (SRB). Those will be collected at baseline and immediately after the intervention.

The ODI questionnaire is one of the instruments for measuring disability caused by LBP. The Slovenian version of the ODI questionnaire is a reliable and valid instrument for assessing outcomes of physical therapy in patients with chronic non-specific LBP [18]. IPAQ was developed as an instrument for cross-national monitoring of physical activity and inactivity and has reasonable measurement properties for monitoring population levels of physical activity among adults in diverse settings aged 18–65 years [19]. Pain intensity is frequently measured on an 11-point pain intensity numerical rating scale, where 0 means no pain and 10 is the worst possible pain. On average, a reduction of 2 points or a reduction of approximately 30% in the NRS is considered a clinically important difference [16, 20].

TUG test, sit to stand test, CSR and 6MWT are part of the Senior Fitness Test battery [21]. Specifically, the tests measure the level of physical abilities (strength, endurance, agility) that are impaired in patients with CLBP.

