## Data processing and statistical analyses

All data related to the study will be stored with the highest possible level of security. Questionnaire data, functional tests results, and exercise session diaries are typed into a database for subsequent transfer into SPSS for reporting and statistical analysis. All statistical analysis will be based on an intention-to-treat basis [27]. The investigator performing the analyses is blinded to treatment allocation. Data analysis will be performed using SPSS v19 (IBM Inc., Armonk, NY, USA).

The normality of distribution will be examined for all variables and those found to have a non-normal distribution will be properly transformed before further analyses. For primary and secondary outcome scores, the mean ± SD, median and range will be given for continuous data. Comparison of pre-intervention parameters of the two groups will be determined using two sample unpaired t-test. Differences between groups in the categorical outcome variable (IPAQ) at each time point (baseline, after treatment, and six-month and 12-month follow-ups) will be analyzed using the χ^2^ test and odds ratio. Analysis of variance with repeated measures will be used to identify changes of the functional outcome variables between baseline and after therapy.

For all tests, a *P* value < 0.05 will be considered significant. The minimal clinically important differences within and between groups comparisons are defined as ≥ 30%.

There will be no interim analyses. Only the authors of the protocol and study designers, SP and NŠ, will have access to all data during the intervention.

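### The 80% power claimed for 40 per group holds only if no outcome is lost, because 40 per group is everyone randomised, and 40 cannot be reproduced from the 30% threshold

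*Protocol article*

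**What the plan says.** All references are to the protocol article.

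- Trial design and study setting describes a "superiority RCT with parallel-group design allocating patients 1:1" and gives the total: "We intend to allocate 80 adults, aged 30–60 years, into two groups".
- Sample size and sampling procedure bases the size on "clinically important improvements in patient measures through an anchor-based approach", set at 30% or more. It names 80% power and concludes "Thus, the inclusion of at least 40 patients per group is planned". Randomisation is by "picking one envelope out of 80, 40 of each option".
- Primary outcome measures lists three questionnaires (ODI, IPAQ, NRS), taken up to 12 months after the intervention, and seven functional tests, taken at baseline and immediately after it. For pain it states that "a reduction of 2 points or a reduction of approximately 30% in the NRS is considered a clinically important difference".
- Data processing and statistical analyses gives a 0.05 significance level without saying one- or two-sided. It reuses the threshold: "The minimal clinically important differences within and between groups comparisons are defined as" 30% or more.
- Recruitment says that participants may withdraw freely and that a patient whose pain exacerbates discontinues the programme.

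The sample-size section names no outcome, SD, baseline mean, control responder rate or loss allowance.

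**The concern.** Two things do not fit together.

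First, the number offered as the minimum for 80% power is also the ceiling set by the envelopes. Nothing lies between the number randomised and the number needed, although the plan itself foresees withdrawal and follows three of its primary measures for a year after treatment.

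Second, the section moves from 30% and 80% power to 40 per group as if one implied the other. The article uses 30% in more than one sense: as a change in a score, and as a threshold for both within-group and between-group comparisons. These senses lead to very different sample sizes.

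The stake is how a null result is read. It would be reported as coming from a trial with 80% power, without saying for what difference and without noting that the power at 6 and 12 months depends on how many patients are still observed.

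**Working it through.** **Inputs from the article:** two arms, 1:1, superiority; 80% power; 40 per arm; 80 envelopes; significance level 0.05; a 30% threshold. **Assumed, because not stated:** two-sided testing, baseline means, SDs, control responder rates and loss rates.

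**1. Trying to reproduce 40.** For two means, n per arm = 2(1.960 + 0.842)² / (Δ/SD)². The article gives no Δ/SD, so the formula cannot be completed. Run backwards, 40 per arm gives Δ/SD = (1.960 + 0.842) × √(2/40) = 2.802 × 0.2236 = 0.626. The exact t-test value is 0.634.

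**2. What 30% would require under each reading (80% power, two-sided 5%).**

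*(a) A 30-point difference in responder proportions.* n = [1.960√(2p̄(1−p̄)) + 0.842√(p₁(1−p₁) + p₂(1−p₂))]² / 0.30². For 30% v 60%: (1.960 × 0.7036 + 0.842 × 0.6708)² / 0.09 = (1.379 + 0.565)² / 0.09 ≈ 42.

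| Control v other arm | n per arm |
|---|---|
| 10% v 40% | 32 |
| 20% v 50% | 39 |
| 25% v 55% | 41 |
| 30% v 60% | 42 |
| 35% v 65% | 43 |

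*(b) A 30% relative difference in mean NRS.* Δ = 0.30 × baseline; t-test n per arm:

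| Assumed baseline | SD 1.5 | SD 2.0 | SD 2.5 |
|---|---|---|---|
| 3 | 45 | 79 | 123 |
| 4 | 26 | 45 | 70 |
| 5 | 17 | 29 | 45 |
| 6 | 12 | 21 | 32 |

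Six of the twelve cells need fewer than 40 and six need more.

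*(c) A difference of 2 NRS points between arms.* The t-test needs 17 per arm at SD 2 and 26 at SD 2.5.

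So 40 is close under (a), may be too many or too few under (b), and is ample under (c). The article does not say which applies.

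**3. Effect of loss.** Take 40 per arm as the number that gives 80%. Power with n analysed is approximately Φ(0.626 × √(n/2) − 1.960). For n = 32: 0.6265 × 4 − 1.960 = 0.546, so about 0.707. The exact t-test gives slightly less:

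| Assumed loss | Analysed per arm | Power for 0.634 SD |
|---|---|---|
| 0% | 40 | 80% |
| 5% | 38 | 78% |
| 10% | 36 | 76% |
| 15% | 34 | 73% |
| 20% | 32 | 70% |

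With 32 per arm, the difference detectable with 80% power rises to 0.71 SD. For a comparison of means these figures do not depend on the SD, because the difference is expressed in SD units.

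**The case against.** The best defence has four parts.

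- **The article is a condensation.** It cites sources for the threshold and for the size, and those or a full protocol may hold the calculation. This stands. A missing SD or outcome would not be a finding by itself.
- **The minimum is stated for inclusion, not for analysis.** Enrolling 40 per arm satisfies it literally. That is true of the wording, but the 80% is attached to this same number with no allowance between enrolment and analysis. Intention-to-treat does not supply outcomes that were never observed.
- **There may be slack.** If the target is 2 NRS points, power with 32 per arm analysed is still 98% at SD 2 and 88% at SD 2.5. This also stands, but the article does not say that this is the target.
- **The loss problem is limited.** No loss rate is given, 5% loss costs only about 2 percentage points of power, and losses between 10 weeks and 12 months touch only ODI, IPAQ and NRS, since the functional tests end with treatment. All of this stands and bounds the size of the point.

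A reader might be tempted to go further in four directions, none of which the document supports. One might infer that 40 is an arithmetic error or too small, but several plausible readings give 40 or fewer. One might say that 30% is only a within-patient criterion, but the analysis section expressly applies it between groups as well. One might say that only a large difference can be detected, but 0.63 SD lies between the conventional medium (0.5) and large (0.8) values. And one might quote power under a multiplicity correction across the ten primary measures, but the article specifies none, so such a figure would not describe this plan.

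**Conclusion.** The point holds in a limited form and should be fixed. The stated minimum equals the number randomised, so on the natural reading the 80% is the power with complete data. Under assumed losses of 5% to 20% it falls to between about 78% and 70% for the same difference. This rests on two-sided 5% testing, a comparison of two means, and 40 being the number that just gives 80%. If 40 already contained slack, the fall would be smaller, but the article does not say so.

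Separately, 40 per group cannot be verified from the 30% threshold, because the article uses that threshold in different senses and ties it to no outcome. That makes the figure unverified. It does not show that the trial is underpowered.

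**What to change.** Leave N at 80 and change the wording in Sample size and sampling procedure.

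1. Say which outcome and time point the 40 refers to, and whether 30% there means a relative difference in means, a difference in responder proportions, or something else. Give the SD or control rate used, with its source.
2. Restate the power, for example: *With 40 per arm analysed, the trial has 80% power (two-sided 5%, t-test) to detect a between-group difference of 0.63 SD. If 5%, 10%, 15% or 20% of patients are lost (assumed range; 38, 36, 34 or 32 per arm analysed), power for that difference is about 78%, 76%, 73% or 70%. With 32 per arm, the detectable difference is 0.71 SD.* If step 1 settles on responder proportions, give the matching figures for that test.
3. Replace the wording of a minimum per group with a plain statement that 40 per arm are randomised.

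The cost is wording only and a less favourable power statement. No patients are added, which matters because recruitment began in May 2018.
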